**Methods:**

We designed an open-label, multi-center 1:1 randomized behavioral trial to test whether a previously validated self-efficacy enhancing breastfeeding intervention can improve breastfeeding duration and/or exclusivity, and lower postpartum blood pressure at 12 months. Randomization is computer-generated and stratified by site (four hospitals in Montreal, Quebec and one hospital in Kingston, Ontario; all in Canada). Included are breastfeeding participants with HDP (chronic/gestational hypertension or preeclampsia) who delivered a live singleton infant at > 34 weeks, speak English or French, and have no contraindications to breastfeeding. Informed and written consent is obtained at hospitalization for delivery or a re-admission with hypertension within 1 week of discharge. Participants assigned to the intervention group receive a breastfeeding self-efficacy-based intervention delivered by a trained lactation consultant in hospital, with continued reactive/proactive support by phone or text message for up to 6 months postpartum. Regardless of group assignment, participants are followed for self-reported outcomes, automated office blood pressure, and home blood pressure at several time points with end of follow-up at 12 months.

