## Background

### Long-term cardiovascular risk after hypertensive disorders of pregnancy

Hypertensive disorders of pregnancy (HDP), including chronic hypertension in pregnancy, gestational hypertension and preeclampsia/eclampsia [1] complicate up to 10% of pregnancies worldwide and are significant causes of severe maternal and neonatal morbidity and mortality [2]. Preeclampsia, the most severe HDP, is a complex clinical syndrome characterized by maternal hypertension and other adverse conditions associated with widespread endothelial activation and dysfunction [1, 2]. There is now overwhelming evidence from large observational studies that HDP not only impacts short-term maternal and neonatal health, but are sex-specific risk factors for premature cardiovascular disease, conferring a 3.7-fold increase in the risk of chronic hypertension, a 4.2-fold increase in risk of heart failure, a 1.8-fold increased risk of stroke, and a 2-fold increased risk of premature ischemic heart disease compared with similar individuals with normotensive pregnancies [3]. This risk is apparent at a median of 10–15 years post-affected delivery [4, 5]. Whereas cardiovascular disease risk is partly mediated by the development of hypertension and metabolic syndrome [6–9], there is evidence of persistent subclinical endothelial dysfunction for months to years following pregnancy affected by HDP, contributing to accelerated vascular impairment [10–13] (Fig. 1). The postpartum period has thus been identified as a critical opportunity to implement targeted screening and positive health interventions for those affected by HDP, and contemporary clinical practice guidelines now encourage systematic assessment of cardiovascular risk post-HDP [14, 15].

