## Methods

### Study objectives and hypotheses of sheMATTERS

The overall aim of the sheMATTERS (iMproving cArdiovascular healTh in new moThERS) trial is to assess the impact of an individualized BSEI on postpartum blood pressure and breastfeeding rates among patients with HDP who initiated breastfeeding. Longer-term (15-year) post-trial follow-up of study participants will additionally be conducted, to observe whether breastfeeding support, and breastfeeding duration/intensity helps to lower the incidence of chronic hypertension or other cardiovascular risk factors, as well as heart disease, stroke, and other long-term health issues among those with HDP (Fig. 3).

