### sheMATTERS trial hypotheses

The primary study hypotheses are that 1) individuals with HDP who receive the BSEI will have lower BP (approximately 5 mmHg systolic and/or 2 mmHg diastolic) compared to those who do not breastfeed, and 2) individuals with HDP who receive the BSEI will have a lower demand for antihypertensive treatment at 12 months postpartum compared with those who receive usual postpartum care. The secondary hypotheses are that:there will be a modest (10–20%) relative benefit in breastfeeding outcomes among participants with HDP who receive the BSEI compared to those who receive usual postpartum care;there will be a lower rate of metabolic syndrome in participants with HDP who receive the BSEI compared to those who receive usual postpartum care, and a greater difference when compared to those who do not breastfeed;rates of breastfeeding duration and exclusivity will be correlated with a greater tendency towards more cardioprotective behaviors over 12 months postpartum;infant neurodevelopment will be positively correlated with longer duration of any breastfeeding;severity of HDP, obesity, markers of inflammation, as well as education level and psychological symptoms at birth will be correlated with breastfeeding duration and exclusivity over 12 months postpartum.

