### Study outcomes

Our primary study endpoint is average systolic and/or diastolic BP, in mmHg, measured by standard recommended technique using validated automated office blood pressure devices. In the case of home blood pressure, an average of four daily measurements over a one-week period is used, after discarding the first day of measurement. Blood pressure data is collected at baseline, 6 weeks, 3 months, 6 months, and 12 months postpartum with the primary outcome at 12 months with repeat blood pressure and other cardiometabolic markers, as well as novel biomarkers. The purpose of the latter measurement is a secondary aim of sheMATTERS, which is enhanced cardiovascular phenotyping of those with HDP.

Our secondary study endpoint includes 1) elevated blood pressure (displayed automated mean blood pressure > 135 mmHg systolic and/or > 85 mmHg diastolic) or use of/increase in previous use of antihypertensive drug therapy, and 2) the presence of metabolic syndrome [83]. An additional secondary endpoint is systolic and/or diastolic blood pressure at 6months postpartum.

Breastfeeding outcomes include the duration of exclusive breastfeeding (in weeks), total breastfeeding duration (in weeks), the proportion of participants exclusively breastfeeding at 6 months, and the proportion of participants continuing any breastfeeding at 6 months and 12 months. Given high rates of in-hospital formula supplementation of breastfeeding infants born to persons with HDP [50], we have defined exclusive breastfeeding as the provision of nothing but breastmilk (either at the breast or via milk expression) after the first 7 days of life.

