### Statistical analysis

Descriptive statistics will be used to characterize the study population. We will compare baseline characteristics in the experimental study arms to assess randomization effectiveness. We will assume two-sample tests such as chi-square tests, t-tests, and non-parametric tests as appropriate to assess between-group differences in various characteristics and outcome measurements. They include proportion on antihypertensive drug therapy, proportion of EBF at 6 months, total breastfeeding duration in weeks, total EBF in weeks, metabolic syndrome, as well as differences in physical activity and dietary patterns. Differences in the primary outcome between the intervention and control groups on study outcomes will be assessed using an intent-to-treat approach. To examine the effect of BSEI on systolic and/or diastolic BP at 12 months, we will use generalized linear regression (GLM) to model for continuous BP readings and the Generalized Estimating Equation (GEE) analyses using logistic regression (reduction of 5 mm in SBP from the baseline vs. no change). We will calculate beta estimates with 95% confidence intervals (CIs) after adjusting for any observed between group differences despite randomization. Given that we plan to recruit non-breastfeeding parents (*N* = 45), we will model breastfeeding first as a continuous exposure variable (number of weeks) with systolic BP as the outcome in a multivariable linear regression model. We will also evaluate the dose-response of breastfeeding categories (i.e., none, < 3 months, < 6 months, > 6 months) to determine systolic and diastolic BP trajectories. In a sensitivity analysis, we will use different combinations of systolic blood pressure and diastolic blood pressure, and delta change in BP from baseline will be assessed. Breastfeeding duration will be divided into quintiles/quartiles, and those will be correlated with a series of BP measures. We will also perform a survival analysis modeling time to cessation of exclusive breastfeeding in both study groups. The model will incorporate interval censoring and compare differences between groups controlling for variables of interest, such as baseline self-efficacy score, maternal education, income, and age. Kaplan-Meir curves and cox-regression will be used to address these aspects.

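### Women with chronic hypertension are eligible, but the article scores antihypertensive drug need in two conflicting ways, one of which counts unchanged or reduced pre-pregnancy treatment as an event

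*Protocol article*

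**What the plan says.** Eligibility covers chronic hypertension. The abstract states: "Included are breastfeeding participants with HDP (chronic/gestational hypertension or preeclampsia". The Background defines the condition in the same way: "Hypertensive disorders of pregnancy (HDP), including chronic hypertension in pregnancy, gestational hypertension and preeclampsia/eclampsia".

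Drug need is part of the primary objective. It is also the second primary hypothesis, that women given the intervention "will have a lower demand for antihypertensive treatment at 12 months postpartum". In Study outcomes it is one half of a secondary composite. The first half is "displayed automated mean blood pressure > 135 mmHg systolic and/or > 85 mmHg diastolic", which is status at the time of measurement. The second half is "use of/increase in previous use of antihypertensive drug therapy". No reference time for previous use is given.

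The Statistical analysis section lists the variables for the two-sample tests: "They include proportion on antihypertensive drug therapy". It makes no allowance there for women treated before pregnancy.

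Randomisation is stratified by site only. Adjustment is for whatever differences between the groups are seen after randomisation. Parity and gestational age are named as examples of characteristics for stratified analysis, and site-specific analyses are planned.

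The 15-year follow-up is to observe whether breastfeeding support and duration "helps to lower the incidence of chronic hypertension or other cardiovascular risk factors".

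**The concern.** The enrolled group mixes women whose hypertension began in pregnancy, and may resolve, with women who had it before. A woman in the second group may be on the same drug at 12 months as before she conceived. Whether she is an event depends on which section of the article the analyst follows. If she is an event, so is a woman whose regimen has been reduced but not stopped, and an improvement is then recorded as a failure.

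Such events would occur at much the same rate in both arms. They raise both event rates, pull the risk ratio towards 1 and add variance. Chance imbalance in chronic hypertension would add noise, because site is the only stratification factor and the only stated adjustment is chosen after looking at the data.

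**Working it through.** **Step 1: the rules side by side.** The phrase in Study outcomes can be read in two ways. Literally, any use is an event and the clause on increase adds nothing. Restrictively, the events are new use, or an increase for women already treated.

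| Woman at 12 months | Study outcomes, literal | Study outcomes, restrictive | Statistical analysis |
|---|---|---|---|
| Treated before pregnancy, unchanged | event | no event on drug component | event |
| Treated before pregnancy, reduced but not stopped | event | no event on drug component | event |
| Treated before pregnancy, increased | event | event | event |
| Untreated before pregnancy, now treated | event | event, if previous means before pregnancy | event |

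The first two rows change sides. The last row shows why the reference time matters. If previous meant the delivery stay, a woman started on a drug then and still on it unchanged would be a non-event on the restrictive reading.

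**Step 2: size.** The plan has no figure to reproduce here. Its sample size section rests on 5 mmHg and on breastfeeding rates, and no drug-use rate or chronic-hypertension share is given.

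From the Sample size calculation section: 278 randomised and 30% loss, so 278 × 0.70 / 2 = 97.3, taken as 97 per arm.

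Assumed: a share c of 10%, 20% or 30% treated before pregnancy, all still treated at 12 months in both arms; drug need in the others of 20% (control) and 10% (intervention); two-sided 5% test.

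Any-use rate = c + (1 − c)p. Power = Φ(difference / SE − 1.96), with SE = √{[p₁(1 − p₁) + p₂(1 − p₂)] / n}.

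For c = 20%: control 0.20 + 0.80 × 0.20 = 0.36; intervention 0.20 + 0.80 × 0.10 = 0.28; SE = √[(0.2304 + 0.2016) / 97] = 0.0667; 0.08 / 0.0667 − 1.96 = −0.76; power 22%.

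| c | Control | Intervention | Risk ratio | Power, any use, n = 97 | Power, only women not already treated, n = 97(1 − c) |
|---|---|---|---|---|---|
| 0 | 20% | 10% | 0.50 | 50% | 50% |
| 10% | 28% | 19% | 0.68 | 32% | 46% |
| 20% | 36% | 28% | 0.78 | 22% | 42% |
| 30% | 44% | 37% | 0.84 | 17% | 38% |

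The risk difference shrinks only from 10 to 9, 8 and 7 points. The rest of the power loss comes from the higher event rates.

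**Step 3: the proposed rule.** It keeps prior users and counts only an increase, at rate e, so the event rate is (1 − c)p + c·e. For c = 10%, 20% and 30%:
- e = 20% versus 10%, as in the other women: power stays at 50%.
- e = 0 in both arms: 46%, 41%, 36%.
- e = 10% in both arms: 43%, 37%, 30%.

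A less favourable case, e = 20% in both arms with c = 30%, gives rates of 20% versus 13% and power 26%, still above the 17% under any use.

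**Step 4: other assumptions.** Take need of 30% versus 15% in the others, and let only 80% of the chronic-hypertension group be fixed events, so the rate is (1 − c)p + 0.8c. The rates are 35.0% versus 21.5%, 40.0% versus 28.0% and 45.0% versus 34.5%. The risk ratio goes from 0.50 to 0.61, 0.70 and 0.77. Power, with pooled variance under the null, falls from 71% to 55%, 42% and 32%. The direction is the same and the loss is somewhat smaller in relative terms.

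**The case against.** The strongest reply is that Study outcomes does consider prior users. A clause about an increase can apply only to women already on drugs, and its natural reading is new use or escalation. That stands. A reader might infer that the plan counts all women alike throughout, but Study outcomes does not say so. The fault is an ambiguous phrase without a reference time, and a different variable in the analysis section.

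It can also be said that any use at 12 months is a legitimate measure of need, and that the two sections may intend two variables. This stands in part, and is a reason to keep any use as a sensitivity analysis. It does not tell the analyst which version answers the objective.

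Parity and gestational age are given only as examples, and a full covariate list may sit in an analysis plan that is not shown. So the absence of hypertension type from that list is no finding in itself. What the article does fix is adjustment chosen from observed imbalances.

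Three stronger inferences are tempting and not supported:
- That the intervention cannot prevent these events. Nothing in the documents rules out treatment being stopped by 12 months.
- That the comparison is biased towards one arm. Randomisation balances chronic hypertension in expectation.
- That the trial has a flawed incident-hypertension endpoint. Incidence appears only as an aim of the 15-year follow-up, where restriction to women at risk is routine detail.

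Finally, the magnitude rests on assumed inputs and models the drug component alone, not the composite. Power would be only about 50% on those inputs with no chronic hypertension at all. The primary endpoint in Study outcomes, continuous blood pressure, does not depend on how drug use is scored.

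**Conclusion.** The point holds as an inconsistency within the article that should be resolved. Chronic hypertension is eligible, and the analysis variable counts unchanged or reduced pre-pregnancy treatment as an event, where the restrictive reading of the endpoint does not.

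The consequence is lost sensitivity in the drug-need comparison. On the main assumptions (10-30% treated before pregnancy and all still treated, 20% versus 10% need in the others, 97 per arm), the risk ratio moves from 0.50 to 0.68-0.84 and power from about 50% to 32-17%. Counting only an increase for prior users gives roughly 30-50% over most of the escalation rates tried. The true size cannot be computed, because the documents give neither the share treated before pregnancy nor any drug-use rate.

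**What to change.** Use one scoring rule in Study outcomes and Statistical analysis, with the pre-pregnancy regimen as the stated reference:
- for women untreated before pregnancy, any antihypertensive use at 12 months is an event;
- for women treated before pregnancy, only an increase over that regimen is an event;
- any use in all women is kept as a sensitivity analysis.

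Pre-specify chronic hypertension or prior antihypertensive treatment as a covariate in the blood pressure and drug-need models, and as a subgroup, in place of adjustment for observed imbalances.

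As a minor point, limit the 15-year incidence aim to women without chronic hypertension at entry.

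The cost is mainly wording, with somewhat fewer events in the drug outcome. The pre-pregnancy regimen must be taken from the medical history and concomitant medication records that Table 2 lists at baseline. Baseline is the delivery hospitalisation, so it should be confirmed that those records capture treatment before pregnancy and not only treatment at delivery.

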### Data collection

The study procedures are shown in Table 2. Study data is collected at baseline (i.e., the delivery hospitalization), 6 weeks, 3 months, 6 months, and 12 months postpartum. All study data is entered by the participants or research staff directly into REDCap, a secure, encrypted web-based electronic data capturing system (www.projectredcap.org). In hospital, participants complete baseline self-report questionnaires either electronically on their cell phone or a Samsung Galaxy Tablet (provided by the research assistant), or on paper. For the subsequent time points, participants are sent electronic links and email reminders to complete their follow-up self-report questionnaires online via REDCap. The research lactation consultants enter all data and clinical notes related to BSEI assessments and interventions directly into the BSEI Activity Logs in REDCap, and breastfeeding-related outcome data are collected via self-report using an infant feeding questionnaire adapted from McQueen et al’s BSE-enhancing intervention pilot trial [81].

**Table 2 Tab2:** sheMATTERS study procedures

Time Point	2	3	4	5	6
	Screening & Baseline	Six Week	Three Month	Six Month	Twelve Month
***Maternal Data***					
**Questionnaires**					
Medical and obstetrical history	**X**				
Maternal characteristics questionnaire	**X**	**X**	**X**	**X**	**X**
Maternal concomitant medications	**X**	**X**	**X**	**X**	**X**
Breastfeeding Self-efficacy Scale (randomized participants only)	**X**	**X**	**X**	**X**	**X**
Healthy Eating Score Questionnaire	**X**		**X**	**X**	**X**
Edinburgh Postnatal Depression Scale	**X**		**X**	**X**	**X**
STAIT/TRAIT Anxiety Scale	**X**		**X**	**X**	**X**
Infant Feeding Questionnaire	**X**	**X**	**X**	**X**	**X**
Maternal Satisfaction Questionnaire (intervention participants only)			**X**	**X**	
**Clinical measures**					
Vital signs (heart rate, respiratory rate, temperature)	**X**				
Blood pressure (SunTech CT40 BP Machine)	**X**			**X**	**X**
Blood pressure (A & D Medical Self-Monitoring BP Machine UA-651)	**X**	**X**	**X**	**X**	**X**
Height, weight	**X**			**X**	**X**
Hip and waist circumference				**X**	**X**
**Biological samples**					
Blood draw for Clinical Laboratory Tests (biochemistry, lipid profile, thyroid profile, microalbumin profile)	**X**			**X**	**X**
Additional 4 ml blood draw for Biomarker Analysis (endothelial and inflammatory markers, circulating plasma micro-RNA)	**X**				**X**
Random Urine, Routine Urinalysis				**X**	**X**
***Infant Data***					
Infant medical data	**X**		**X**	**X**	**X**
Ages and Stages Questionnaire – 3rd Edition					**X**

To collect socio-demographic and maternal health information, participants complete the Maternal Characteristic Questionnaire at each time point (see Additional file 1). We are using the self-report Edinburgh Postnatal Depression Scale (EPDS) [84] and State-Trait Anxiety Inventory (STAI) [85] to assess postpartum depression and anxiety, respectively, at baseline, 3 months, 6 months, and 12 months postpartum. Previous norms indicate that total scores of 10 or above on the EPDS and 50 or above on the STAI are consistent with clinically relevant depression and anxiety, respectively [86]. The Breastfeeding Self-Efficacy Scale (BSES), a validated 33-item questionnaire, captures information on the participant’s breastfeeding techniques, beliefs and attitudes using a 5-point Likert scale for each item [87]. Breastfeeding outcomes are captured by the Infant Feeding Questionnaire (IFQ), which collects detailed information on duration and exclusivity of breastfeeding, reason for supplements, satisfaction, and any difficulties [88]. The BSES and IFQ are sent to participants at every time point or until the cessation of breastfeeding is reported. For the intervention group, an evaluation of participants’ satisfaction with the intervention using the modified satisfaction questionnaire from [name]’s WISE trial, is sent at 3 months and 6 months. Self-reported physical activity is collected at 3 months, 6 months and 12 months using the validated International Pregnancy Physical Activity Questionnaire (PPAQ) [89]. The Healthy Eating Score, a newly developed composite score assessing adherence to the Canada Food Guide [90], is being used to assess quality and variety of the diet at baseline, 3 months, 6 months, and 12 months postpartum. Lastly, at 12 months, parents complete the Ages and Stages Questionnaire, Third Edition (ASQ-3) [91], which has shown to be a reliable and valid instrument for determining the need for further infant developmental evaluation [92, 93].

Maternal and infant medical data is collected by research assistants via medical records reviews at baseline and recorded on our Maternal or Infant Clinical Measures Form (CMF). At subsequent time points, the Maternal CMF documents current health status and cardiovascular health, and the Infant CMF documents the child’s health and growth (see Additional files 2 for Maternal CMFs and 3 for Infant CMFs). Clinical measures are obtained by research staff during postpartum hospitalization (BP and weight) and clinic follow-up visits at 6 months and 12 months (BP, weight, hip and waist circumference). BP is measured using the same validated automated office blood pressure device (SunTech CT40 BP machine) at each site. All members of the research team are trained in proper technique of blood pressure measurement, as recommended by Hypertension Canada (https://guidelines.hypertension.ca/). Briefly, blood pressure measurement is taken with appropriately sized cuffs, in the seated position with legs uncrossed and arms positioned at the level of the heart, in a quiet room. Five measurements are taken with a one-minute interval between each, and an average of measurements is displayed by the machine.

At baseline, all participants are loaned a home BP monitor (LifeSource® A&D Medical) and provided with a web-based, Bluetooth-enabled, encrypted smartphone application (Sphygmo™) to enable remote transmission of their BP measures to the research team. A member of the research team provides instructions on how to measure and transmit their BP at home (ideally twice in morning, twice in the evening daily for 1 week prior to each scheduled study follow-up). The research team assists with installation of the mobile app prior to hospital discharge. Participants receive an automatic email about 10 days prior to the data collection time-point as a reminder to take their blood pressure and complete the online questionnaires. In addition, text messages via a mobile app are sent to participants a few days after the original email as a second reminder to take their blood pressure. The study coordinator tracks adherence of BP monitoring through the Sphygmo™ app as an end-user.

Blood and urine samples are collected for a routine metabolic panel at 6 months and 12 months, as part of usual postpartum care of those with HDP. A comprehensive metabolic panel is conducted in accordance with local laboratory protocols, and analyzes the following: glycosylated hemoglobin, fasting glucose, lipid profile [includes total cholesterol, non-HDL cholesterol, triglycerides, calculated LDL cholesterol], urine analysis, urine microalbumin to creatinine quantification, serum creatinine, serum electrolytes [sodium, potassium, chloride, bicarbonate, calcium], apolipoprotein-B. At baseline and at 12 months postpartum, we also collect an additional four ml of blood to process for analysis of HDP biomarkers (angiogenic factors, inflammatory factors, circulating plasma micro-RNA). Samples for biomarker analysis (serum and plasma) are kept frozen (− 80 °C) at a local freezer until the end of the recruitment period and will then be shipped on dry ice in batches directly to the laboratory for analysis (see Additional file 6: Appendix 3).

If participants are not able to attend the follow-up clinic visits in person, clinical data can be collected remotely. The study physician will schedule a meeting with the participant via ZOOM™ to conduct the post-HDP follow-up assessment. All participants are provided with a measuring tape upon enrollment for self-measurement of waist and hip circumference, and participants can self-report their weight using their own scales. BP measurements will be obtained remotely using the participants’ home BP monitoring machine loaned to them at recruitment. The participants will also be emailed a requisition for biospecimen collection (blood, urine) that can be conducted at their local walk-in health centers.

Finally, participants who consent will also participate in pragmatic long-term follow-up via data linkage to ascertain cardiovascular outcomes (Fig. 3).

